**2 GENERAL DESIGN**

**2.1 Overall Design**

This is an open, block-randomised, comparative, multicentric study.

All subjects presenting at the outpatient clinic or admitted in the ward of the Maprik Hospital and Yagaum Health Center who are diagnosed with malaria (history of fever and no other major symptom, OptiMAL test positive) and have been already treated for malaria in the last 28 days can be included if they give their informed consent and if the clinician in charge would have given the standard treatment for resistant malaria in the absence of the study. A patient should not be included if the clinician prefers to use quinine for whatever reason, if the patient has one of the symptoms or signs of complicated or severe malaria (i.e. history of recent convulsion, any neurological sign or impairment of consciousness, temperature >40 C0, heavy vomiting, haemoglobinuria, respiratory distress, bleeding, circulatory collapse, shock, jaundice, haemoglobin < 5 g/dl), has contra-indications for mefloquine (history of psychiatric disorder, epilepsy), is less than 6 months of age, or is pregnant. The patients will be randomised on the spot to have either Cotrifazid, Lariam or standard treatment (at present quinine + Fansidar). The treatment dosage and schedule for Cotrifazid will be the following : subjects > 40 kg : 2 x 2 tablets, subjects < 40 kg and > 20kg : 2 x 1 tablet, subjects < 20 kg : 2 x ½ tablet, ever 12 hours for 7 days. The treatment dosage and schedule for Lariam will be the following : subjects > 60 kg : 6 tabs (3 at hour 0, 2 at hour 8, 1 at hour 24), subjects > 40 kg and < 60 kg : 5 tabs (2, 2, 1), subjects < 40 kg and > 30 kg : 3 ½ tabs (1 ½ , 1, 1), subjects < 30 and > 20 kg : 3 tabs (1, 1, 1), subjects < 20 kg and > 10 kg : 1 ½ tabs ( ½ , ½, ½ ), subjects < 10 kg : ¾ tablet ( ¼ , ¼, ¼ ). Follow-up assessments will be done at hours 24, 48 and 72 (clinical, parasitological and pharmacological), and days 7 (clinical, parasitological, biochemical, and pharmacological) and 14 (clinical, parasitological, haematological, and pharmacological), or more intensively in case of persisting symptoms or pathological signs. Treatment will be changed to the standard treatment (at present quinine + Fansidar) if necessary (problems of tolerance, aggravation of clinical status, increase in parasitaemia etc).

All blood samples will be taken by venepuncture (2 ml).

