**5.1.1.3 Duration**

Cotrifazid will be given for 7 days.

Lariam will be given for 24 hours.

Quinine will be given for 5 days.

Fansidar will be given as a single dose at day 0.

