**5.1.1.4 Dispensing of Trial Drug**

The administration of the drug for the first three days will be supervised by the nurse in charge of the trial.

All drug supplies are to be returned to Fatol Arzneimittel GmbH.

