**6 WITHDRAWAL**

**6.1 Conditions for Withdrawal**

1. Failure of the subject to attend scheduled visits.
2. Adverse events (including intercurrent illnesses).
3. Occurrence of complications - if Cotrifazid or Lariam, change to standard treatment, if quinine + Fansidar, persist with standard treatment (including other available drugs as considered clinically appropriate)
4. Violations of, and deviations from, the protocol.
5. Subject withdraws consent.
6. Subject lost to follow-up.
7. Administrative/other.

***Subjects may withdraw from the trial at any time and for any reason, without affecting their right to treatment by the investigator****.* The investigator has the right to withdraw a subject for any reason which is in the best interests of the subject, including intercurrent illness, adverse events, or treatment failure.

Although withdrawals should be avoided if at all possible, it is understood that withdrawals may occur during a trial. Whenever a subject is withdrawn from a trial, FOR WHATEVER REASON, a final trial evaluation must be completed for that subject, stating the reason for withdrawal. All documentation concerning the subject must be as complete as possible.

Withdrawals due to non-attendance must be followed up by the investigator to obtain the reason for non-attendance.

WITHDRAWALS DUE TO INTERCURRENT ILLNESS OR ADVERSE EVENTS MUST BE FULLY DOCUMENTED IN THE CASE RECORD FORM, WITH SUPPLEMENTARY INFORMATION WHERE AVAILABLE AND/OR APPROPRIATE.

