**9 SUBJECT ANALYSIS POPULATIONS**

All subjects who are randomised to receive either Cotrifazid or the comparators constitute the ‘*intention to treat population’*.

Subjects will be excluded from analysis of *safety* if they do not receive at least one daily dose of Cotrifazid or comparators, and one follow-up visit. Remaining subjects constitute the ‘*safety population’.*

Subjects will be excluded from final analysis of *efficacy* if they do not receive the full dose of Cotrifazid, or the full dose of Fansidar + at least 3 daily dose of quinine, and one follow-up visit. Remaining subjects constitute the ‘*efficacy population’*.

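### The efficacy population drops Cotrifazid patients switched to standard treatment before day 7 instead of counting them as failures, and it states no condition for Lariam

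*Protocol*

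**What the plan says.** Section 9 of the protocol defines three sets. The intention-to-treat set is everyone randomised: "All subjects who are randomised to receive either Cotrifazid or the comparators constitute the" that population. The efficacy set is narrower. Patients leave the final efficacy analysis "if they do not receive the full dose of Cotrifazid, or the full dose of Fansidar + at least 3 daily dose of quinine", and they also need one follow-up visit. The section names no dose condition for Lariam.

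Section 5.1.1.3 fixes the courses: "Cotrifazid will be given for 7 days", quinine runs for 5 days, Fansidar is a single dose, and "Lariam will be given for 24 hours".

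Section 2.1 provides for a change of treatment: "Treatment will be changed to the standard treatment (at present quinine + Fansidar) if necessary". Its reasons include poor tolerance, worsening clinical status and increasing parasitaemia. Section 6.1 adds, among the conditions for withdrawal, "Occurrence of complications - if Cotrifazid or Lariam, change to standard treatment"; patients already on quinine + Fansidar stay on standard treatment.

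Section 10.1 states the hypothesis as non-inferiority of the Cotrifazid cure rate to mefloquine or to quinine and Fansidar. Section 10.4.1.1 makes treatment failure and complications primary comparisons.

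**The concern.** The events that trigger a switch are largely the events the primary comparison is meant to count. A Cotrifazid patient who worsens on day 2 and is switched has not had the full Cotrifazid course, so section 9 takes that patient out of both numerator and denominator. Being analysed then depends on the outcome.

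The rule is also uneven. Cotrifazid patients must complete all 7 days. Standard-arm patients need the single Fansidar dose and at least three daily doses of a 5-day quinine course, and with complications they remain on their assigned treatment. A standard-arm failure after the quinine threshold therefore stays in and counts. Lariam, one of the two comparators in the hypothesis, has no condition at all, so the efficacy set for that comparison is undefined.

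In a non-inferiority trial, removing failures from the test arm moves the result towards the conclusion the trial hopes to reach.

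**Working it through.** **Inputs from section 10.3.** Comparator success is 95%. The lowest acceptable Cotrifazid success is 86%, which implies a 9-point margin. The test is one-sided with 95% confidence limits, at 80% power, with 110 per arm and 10% loss, so 110 × 0.9 = 99 evaluable per arm.

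**The plan's own figure.** n = 2 × 0.95 × 0.05 × (1.645 + 1.282)² / 0.09² = 100.4 per arm. Allowing for 10% loss gives 110 (× 1.1) to 112 (÷ 0.9). This form uses the quantile for half of beta. The plain one-sided form with 80% power gives 73 before loss. The sample size is not in dispute here; it only sets the scale.

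**Which failures can drop out.** Scheduled assessments are at hours 24, 48 and 72 and at days 7 and 14. Cotrifazid failures switched by hour 72, or at an unscheduled visit before the course ends, are exposed to the rule. Failures found at day 7 or 14 in patients who completed the course are not.

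**Effect on the observed rate.** With true success p and a share f of failures removed, observed success = p / (p + (1 − p)(1 − f)). For p = 0.86:
- f = 0.10: 0.86 / 0.986 = 87.2%
- f = 0.25: 0.86 / 0.965 = 89.1%
- f = 0.50: 0.86 / 0.930 = 92.5%
- f = 0.75: 0.86 / 0.895 = 96.1%

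**Effect on the conclusion.** Non-inferiority is declared when the one-sided 95% Wald limit (unpooled) for the difference in success excludes −9 points. This criterion is taken from section 10.3. The value of f is an assumption; the protocol gives none.

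| Cotrifazid failures removed | Difference, no comparator failures removed | False non-inferiority | Difference, same share removed from comparator | False non-inferiority |
|---|---|---|---|---|
| 0% | 9.0 points | 6% | 9.0 points | 6% |
| 10% | 7.8 | about 10% | 8.3 | 9% |
| 25% | 5.9 | 22% | 7.1 | 15% |
| 50% | 2.5 | 59–60% | 5.0 | 39% |
| 75% | −1.1 | 95–96% | 2.6 | 81–85% |

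Where a range is shown, the lower figure lets exclusions shrink the arm below 99, and the upper figure holds 99 analysed per arm. If the comparator loses failures at half the Cotrifazid rate, the results for 25%, 50% and 75% are about 19%, 49–50% and 90–92%.

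**A drug clearly below the limit.** With true failure of 20% and no comparator failures removed, false non-inferiority is 0.2% with no exclusion, between 2% and 3% with a quarter of Cotrifazid failures removed, and about 20% with half removed.

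**Source of the bias.** At 50% removed, equal exclusion in both arms takes false non-inferiority from 6% to 39% (33 points). Sparing the comparator adds about 20 points more. The larger part comes from excluding failures at all.

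**The case against.** Several points on the other side have force.

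- **The sentence does not tie each dose condition to the assigned arm.** A Cotrifazid patient switched to quinine + Fansidar who then has full Fansidar and enough quinine could be said to meet the second condition and stay in. That reading is possible but less natural. Even on it, no text says the patient counts as a Cotrifazid failure.
- **Lariam.** A reader might infer that every Lariam patient is excluded. That takes literally a sentence which was plainly not meant so. The gap is a drafting omission; it leaves the Lariam set undefined, not empty.
- **The unequal thresholds.** A reader might take the 7-day v three-dose contrast as the main fault. The 39% under equal removal shows that it is the smaller part. Standard-arm patients who stop before the quinine threshold also drop out, so the zero-removal column is the least favourable case.
- **Extent.** A reader might infer that Cotrifazid failures as a whole vanish. Only those switched before the course ends can.
- **The 14% scenario.** Section 10.3 calls 86% success or more acceptable, so this is the boundary of acceptability. For a drug well below it the error is smaller, as shown.
- **Supervision.** "The administration of the drug for the first three days will be supervised", so later Cotrifazid intake is unobserved. The same is true of quinine days 4 and 5, and this adds little.
- **The analysis plan.** Which analyses use the intention-to-treat set may be settled in a statistical analysis plan that is not shown, and its absence from the protocol is no finding. The finding is that section 9 itself ties the final efficacy analysis to a set that removes failures.

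**Conclusion.** The concern holds in this form. Section 9 fixes a rule that, on its natural reading, removes early Cotrifazid failures from the primary failure comparison. It is stricter for Cotrifazid than for quinine and leaves Lariam without a condition. The direction of the bias favours Cotrifazid.

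Its size depends on the unknown share of failures switched before the course ends. At the 14% v 5% boundary, false non-inferiority goes from about 6% to between about 10% (a tenth removed) and 95% (three quarters removed) if the comparator loses none, and to between 9% and about 81–85% if it loses the same share. These figures assume 99 per arm and a 9-point margin tested with a one-sided 95% limit. The protocol does not support a single headline figure, nor the claim that inferiority would always be hidden. Because the rule can change the primary conclusion and is easily corrected, it should be corrected before the analysis.

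**What to change.** Reword section 9; this concerns the analysis only.

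1. In all three arms, keep in the efficacy analysis every patient whose assigned course was incomplete because of lack of efficacy or complications, and count that patient as a treatment failure.
2. State the efficacy-population condition for Lariam, and define the per-protocol set on the same basis in each arm. Equal thresholds without step 1 are not enough.
3. Report the failure comparison in the already defined intention-to-treat population alongside it, and conclude non-inferiority only if both agree.

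The changes need no new visits and no change to treatment; the reason for withdrawal is already recorded under section 6.1. The cost is that the reported Cotrifazid success rate may be less favourable: in the half-removed example, 86% instead of 92.5%. Requiring agreement between two sets can also cost some power.

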Subjects < 10 kg ½ tablet

SCHEDULE Every 8 hours for quinine, hour 0 for Fansidar

ROUTE OF ADMINISTRATION Oral for quinine and Fansidar, or I.M. for quinine

Parameters OF EFFICACY 1. Fever clearance time

1. Parasite clearance time
2. Rate of early and late treatment failure (ETF, LTF)
3. Occurrence of complications

PARAMETERS OF TOLERANCE: 1. Reported Adverse Events (AEs)

2. Clinical and laboratory values

Secondary Parameters of EfficaCY 1. Symptom clearance time

2. Haemoglobin concentration

PROCEDURES

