All subjects who are diagnosed with malaria (history of fever and no other major symptom, OptiMAL test positive) and have been already treated for malaria in the last 28 days can be included if they give their informed consent and if the clinician in charge would have given the standard treatment for resistant malaria in the absence of the study. A patient should not be included if the clinician prefers to use quinine for whatever reason, if the patient has one of the symptoms or signs of complicated or severe malaria(i.e. history of recent convulsion, any neurological sign or impairment of consciousness, temperature >40 C0, heavy vomiting, haemoglobinuria, respiratory distress, bleeding, circulatory collapse, shock, jaundice, haemoglobin < 5 g/dl), is less than 6 months of age or is pregnant. The patients will be randomised on the spot to have either Cotrifazid, Lariam or standard treatment (at present quinine + Fansidar). The treatment dosage and schedule for Cotrifazid will be the following : subjects > 40 kg : 2 x 2 tablets, subjects < 40 kg and > 20kg : 2 x 1 tablet, subjects < 20 kg : 2 x ½ tablet, ever 12 hours for 7 days. The treatment dosage and schedule for Lariam will be the following : subjects > 60 kg : 6 tabs (3 at hour 0, 2 at hour 8, 1 at hour 24), subjects > 40 kg and < 60 kg : 5 tabs (2, 2, 1), subjects < 40 kg and > 30 kg : 3 ½ tabs (1 ½ , 1, 1), subjects < 30 and > 20 kg : 3 tabs (1, 1, 1), subjects < 20 kg and > 10 kg : 1 ½ tabs ( ½ , ½, ½ ), subjects < 10 kg : ¾ tablet ( ¼ , ¼, ¼ ). Follow-up assessments will be done at hours 24, 48 and 72 (clinical, parasitological, pharmacological) and days 7 (clinical, parasitological, biochemical and pharmacological) and 14 (clinical, parasitological, haematological, pharmacological), or more intensively in case of persisting symptoms or pathological signs. Treatment will be changed to the standard treatment (at present quinine + Fansidar) if necessary (problems of tolerance, aggravation of clinical status, increase in parasitaemia etc with Cotrifazid or Lariam).

STATISTICAL ANALYSIS

EFFICACY :

1. Comparison of the fever clearance time in the Cotrifazid and comparator groups
2. Comparison of the parasite clearance time in the Cotrifazid and comparator groups
3. Comparison of the rate of ETF and LTF in the Cotrifazid and comparator groups
4. Comparison of the rate of complications in the Cotrifazid and comparator groups

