**5.2 Assessment of Safety**

**5.2.1 Safety Parameters (including Laboratory Evaluations)**

The prime measurement of safety in this trial is the close observation of the subjects. All subjects will be followed clinically every day for the first 4 days, and longer in case of complication. All subjects will be seen at day 7 and 14 to identify late adverse events or clinical failure.

Laboratory measurements : AST and ALT will be measured at Day 0 and 7, haemoglobin concentration at day 14.

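### The efficacy population drops Cotrifazid patients switched early for failure or a complication, which biases the non-inferiority comparison towards Cotrifazid

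*Protocol*

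**What the plan says.** Section 9 defines three populations. The efficacy population, the only one tied to the final efficacy analysis, excludes subjects "if they do not receive the full dose of Cotrifazid, or the full dose of Fansidar + at least 3 daily dose of quinine"; one follow-up visit is also needed. No dose rule is given for Lariam. An intention-to-treat population of all randomised subjects is defined, but neither section 9 nor section 10 assigns an analysis to it.

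Cotrifazid is taken twice daily for 7 days (sections 5.1.1.1 and 5.1.1.3), which makes 14 doses. Several provisions can interrupt that course:

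- Section 2.1 changes treatment to quinine + Fansidar "if necessary (problems of tolerance, aggravation of clinical status, increase in parasitaemia etc"). The synopsis ties this to the two non-standard arms: "increase in parasitaemia etc with Cotrifazid or Lariam".
- Section 6.1, on complications: "if Cotrifazid or Lariam, change to standard treatment, if quinine + Fansidar, persist with standard treatment (including other available drugs as considered clinically appropriate").
- Section 5.2.1 sets when such changes are most likely to be made: "All subjects will be followed clinically every day for the first 4 days".

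The events behind these changes are efficacy endpoints. The synopsis lists "Rate of early and late treatment failure (ETF, LTF") as an efficacy parameter and plans a "Comparison of the rate of ETF and LTF in the Cotrifazid and comparator groups". Section 5.3.1 makes both failure rate and complications primary. Section 10.1 states the hypothesis as non-inferiority of the Cotrifazid cure rate.

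**The concern.** A patient who fails early on Cotrifazid is switched because the drug failed, and so cannot complete 14 doses. The completion rule then removes him from the analysis meant to count him as a failure. Exclusion is caused by the outcome, so what remains in the Cotrifazid arm is enriched for successes.

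The standard arm is treated differently. A patient there with a complication stays on treatment, with other drugs added if needed, and meets the dose rule after day-0 Fansidar and 3 of the 5 quinine days. Removing test-arm failures raises the observed cure rate and moves the result towards a non-inferiority claim.

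**Working it through.** **Inputs (section 10.3).** Comparator success 95%; lowest acceptable Cotrifazid success 86%, so the margin is 95 - 86 = 9 points; 110 per arm; 10% loss; one-sided test with 95% limits; 80% power. Evaluable per arm: 110 × 0.9 = 99.

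**The protocol's own figure.** With equal true success of 95%, n = 2 × 0.95 × 0.05 × (z₁₋α + z_power)² / 0.09².

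- One-sided 5%, 80% power: n = 73, or 82 after 10% loss.
- The same with z at 0.90 (beta halved, as for equivalence): n = 101, or 112 to 113 after loss, within 3% of the stated 110.

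The planned size is adequate. The problem lies in who is analysed.

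**Can a switched patient complete the course?** At the daily reviews in the first 4 days, at most about half of the 14 doses have been taken. A patient switched then fails the full-dose condition, and nothing in the protocol retains him as a failure.

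**Tipping point (no share assumed).** Section 10.4 names no interval, so I use the one-sided 95% Newcombe lower limit:

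L = (p₁ - p₂) - √[(p₁ - l₁)² + (u₂ - p₂)²],

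where l₁ and u₂ are Wilson limits with z = 1.645. The standard arm is fixed at 94/99 (p₂ = 0.9495, u₂ = 0.9752).

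- 91/99: p₁ = 0.9192, l₁ = 0.8622, L = -0.0303 - √(0.0570² + 0.0257²) = -0.0928. This fails.
- 91/98, one failure excluded: p₁ = 0.9286, l₁ = 0.8733, L = -0.0209 - √(0.0553² + 0.0257²) = -0.0819. This passes.

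| Cotrifazid failures of 99 | L, all kept | Exclusions needed to pass | L after exclusion |
|---|---|---|---|
| 7 | -8.07 | 0 | n/a |
| 8 | -9.28 | 1 | -8.19 (91/98) |
| 10 | fails | 3 | -8.43 (89/96) |
| 12 | fails | 5 | -8.69 (87/94) |
| 14 | -16.28 | 7 | -8.95 (85/92) |

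With an unpooled Wald limit, 8 failures already pass, 9 need one exclusion, and 10, 12 and 14 again need 3, 5 and 7.

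**False non-inferiority (share f assumed).** True success is set at the margin, 86% v 95%. Failures are binomial in 99 per arm, and each Cotrifazid failure is excluded with probability f. The probability that L exceeds -9 points is found by exact enumeration. Analysed Cotrifazid success is 0.86 / (1 - 0.14f), and the expected number excluded is 99 × 0.14 × f.

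| f | Expected excluded | Analysed success | Newcombe: Cotrifazid loss only | Newcombe: same f in standard arm | Wald: Cotrifazid loss only | Wald: same f |
|---|---|---|---|---|---|---|
| 0 | 0 | 86.0% | 4.9% | 4.9% | 5.9% | 5.9% |
| 0.05 | 0.7 | 86.6% | 6.6% | 5.9% | n/a | n/a |
| 0.10 | 1.4 | 87.2% | 8.6% | 7.0% | 10.5% | 8.7% |
| 0.25 | 3.5 | 89.1% | 18.8% | 12.2% | 22.4% | 15.5% |
| 0.50 | 6.9 | 92.5% | 52.4% | 30.2% | 58.8% | 39.0% |

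If the standard arm loses half of f, the Newcombe figures at f = 0.10, 0.25 and 0.50 are 7.8%, 15.3% and 41.5%.

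**The case against.** The strongest contrary points are these.

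- **Per-protocol sets are usual in non-inferiority trials, and intention-to-treat is defined.** Section 10 names no population, and the choice could be settled in an analysis plan. But section 9 does assign the final efficacy analysis, to the set with these exclusions. A per-protocol set should remove non-adherence; stopping because the drug failed is an outcome.
- **The sentence can be read literally.** A switched patient who then takes Fansidar and three days of quinine meets its second limb and stays in. On that reading, however, every unswitched Lariam patient would be excluded, so the rule is evidently meant arm by arm. Even on the literal reading, the patient is kept only because he received the comparator.
- **The asymmetry has limits.** Complications are a withdrawal condition in every arm, and the instruction to persist covers complications only. A standard-arm patient who dies or stops quinine before three daily doses is also dropped. The contrast with Lariam rests on the absence of a rule. All of this stands, and it makes the standard arm the firmer comparison. Equal loss reduces the bias without removing it.
- **The size is unknown.** Failures first acted on at day 7 or 14, after a full course, stay in. Severe malaria is excluded at entry and the first three days of dosing are supervised, so early switches may be few. At f of 5 to 10% the inflation is modest. The single-exclusion reversal is a boundary case that depends on the interval used. This also stands.
- **The events are not lost from the record.** Adverse event reports and the final evaluation remain, so a corrected count could be recovered. That makes the fix easy, but it does not mend the stated rule.

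**Conclusion.** The concern holds, and the rule should be changed before analysis. As written and read arm by arm, section 9 removes primary-endpoint events from the test arm because they occurred, in a comparison where such removal favours the sponsor's hypothesis. The direction does not depend on any assumed share.

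The size does. At a true 9-point deficit, excluding 10 to 50% of Cotrifazid failures raises false non-inferiority from 4.9% to between 8.6% and 52% with no standard-arm loss, or between 7.0% and 30% with equal loss. These figures assume 99 evaluable per arm, the 9-point margin and a one-sided 95% Newcombe limit; a Wald limit gives somewhat higher values and the same pattern.

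**What to change.** Amend section 9 as follows.

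1. In any arm, a patient whose drug is changed or supplemented for lack of effect or a complication stays in the efficacy population as a treatment failure of the assigned arm, whatever number of doses was taken. This is the essential change.
2. Exclude for incomplete dosing only when the reason is unrelated to outcome, under one rule for all three arms including Lariam, for example all doses due up to the visit at which the outcome was reached.
3. Report the cure-rate comparison in the intention-to-treat population as well.

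A change for tolerance alone need not count as failure in the primary test, but it should be handled alike in every arm and its number given per arm. Section 6.1 already requires a final evaluation "stating the reason for withdrawal"; code that reason as lack of effect, complication or tolerance.

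The cost is one paragraph and one coded field, with no extra visits. Cotrifazid's cure rate will look slightly less favourable, and the power that exclusion lent is given up. At true success of 95% in both arms, power is 94% with 25% of Cotrifazid failures excluded and 86% with all kept, or 83% if 5 of the 99 Cotrifazid patients are also left out for tolerance (94 v 99). All exceed the planned 80%. These figures cover item 1 only; in the intention-to-treat report, the handling of losses would lower them.

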**5.3 Assessment of Efficacy**

**5.3.1 Primary Efficacy Parameters**

The primary parameters of efficacy i) fever clearance time, ii) parasite clearance time, iii) failure rate, iv) occurrence of complications, information collected from day 1,2,3, 7 and 14.

Thick and thin blood films will be Giemsa stained and species-specific density will be counted per/200 white blood cells (WBC). Slides will be declared negative if no parasites are seen in 100 thick film fields. Parasite density per microliter blood will be calculated by multiplying the parasitemia/200 WBC by a WBC count of 10000/L in children aged < 5 years and of 8000/L in persons aged > 5 years.

1. **Secondary Efficacy Parameters**

The secondary parameters of efficacy are i) symptom clearance time, information collected at day 1,2,3, 7 and 14, and ii) haemoglobin concentration from samples collected at day 14.

1. **Assessment of Pharmacology**

Pharmacokinetics will be assessed in a small subsample of patients (5). Blood will be drawn (2 ml by venepuncture) at hour 2, 8, 16, 24, 36, 72.

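### Section 9 can drop Cotrifazid patients who fail during the 7-day course from the final efficacy analysis instead of counting them as failures

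*Protocol*

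**What the plan says.** - **Exclusion rule.** Protocol section 9 excludes patients from the final efficacy analysis "if they do not receive the full dose of Cotrifazid, or the full dose of Fansidar + at least 3 daily dose of quinine", and also requires one follow-up visit. It makes no exception for patients who stopped because treatment failed, and it states no dose criterion for Lariam.
- **Length of course.** Section 5.1.1.3: "Cotrifazid will be given for 7 days". Lariam takes 24 hours, quinine 5 days, and Fansidar is a single dose on day 0.
- **Change of treatment.** Section 2.1 changes patients to standard treatment "if necessary (problems of tolerance, aggravation of clinical status, increase in parasitaemia etc". The synopsis has the same list but ties it to the two other arms: "problems of tolerance, aggravation of clinical status, increase in parasitaemia etc with Cotrifazid or Lariam".
- **Complications and failure.** Section 6.1, on complications: "if Cotrifazid or Lariam, change to standard treatment, if quinine + Fansidar, persist with standard treatment". The same section lets the investigator withdraw a patient for reasons "including intercurrent illness, adverse events, or treatment failure".
- **Endpoints.** The synopsis lists "Rate of early and late treatment failure (ETF, LTF") and complications among the main efficacy parameters. Section 5.3.1 makes failure rate and complications primary, with "information collected from day 1,2,3, 7 and 14".
- **Populations and tests.** Section 9 also defines an intention-to-treat population of all randomised patients. Section 10.4.1.1 compares failure and complication rates without naming a population. Section 10.1 states the cure-rate hypothesis as non-inferiority.

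**The concern.** Read together, these sections let the outcome decide who is analysed. A Cotrifazid patient who worsens at hour 24, 48 or 72 and is switched has not had 7 days of drug. Section 9 then takes that patient out of the analysis meant to count the failure. Nothing in the protocol says that such a patient is scored as a failure.

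The arms are not treated alike. A standard-arm patient with the same complication continues the allocated treatment. That patient stays in after full Fansidar, 3 of the 5 quinine days and one visit. Lariam is finished at 24 hours.

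Removing failures raises the observed success rate. If that happens more in the test arm, the observed difference shrinks and a non-inferior verdict becomes easier to reach when Cotrifazid is in truth at the limit of acceptability. The trial is open (section 4.2) and switching is left to judgement, so the clinician who decides on a switch knows the allocation.

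**Working it through.** **1. What happens to a patient with an early event**

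| Arm | Action on a complication (6.1) | Section 9 dose requirement | Analysed for efficacy? |
|---|---|---|---|
| Cotrifazid, event before day 7 | Change to standard treatment | Full 7-day course | No |
| Cotrifazid, event after the full course | Change to standard treatment | Met | Yes |
| Standard | Continue | Full Fansidar, at least 3 quinine days | Yes, unless fewer than 3 quinine days |
| Lariam | Change to standard treatment | None stated | Not settled by the text |

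**2. Plan figures**

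Section 10.3 gives 110 per arm, 95% comparator success, 86% as the lowest acceptable Cotrifazid success, 10% loss, 80% power and a one-sided test. The margin is 95 − 86 = 9 points. Evaluable patients per arm: 110 × 0.90 = 99.

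Sample-size check, with n = 2 × 0.95 × 0.05 × (z_α + z_β)² / 0.09²:
- One-sided 5%, 80% power: 0.095 × (1.645 + 0.842)² / 0.0081 = 72.5, so 73; 73/0.9 gives 82.
- With 1.282 in place of 0.842 (the equivalence-type variant): 100.4, so 101; 101/0.9 gives 113, and 101 × 1.1 gives 112.

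The second form comes close to the stated 110. The sample size is not in dispute here, and 99 per arm is used below.

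**3. Effect of dropping failures**

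Let *s* be the share of Cotrifazid failures that section 9 removes. The protocol gives no value, so *s* is an assumption. With true Cotrifazid success of 86%:
- expected Cotrifazid failures = 99 × 0.14 = 13.9
- expected number removed = 99 × 0.14 × *s*
- apparent success = 0.86 / (0.86 + 0.14 × (1 − *s*))

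The chance of declaring non-inferiority at true rates of 86% and 95% was found by exact binomial enumeration, with each failure removed independently with probability *s*. The decision rule is also assumed, since section 10.4.1.1 names only a one-tailed Mantel-Haenszel test. Cotrifazid is declared non-inferior if the one-sided 95% Wald lower limit of the difference (Cotrifazid minus control) exceeds −9 points. The last column uses the Farrington-Manning score test instead.

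| *s* | Removed | Apparent success | Wald, Cotrifazid only | Wald, control loses *s*/2 | Wald, control loses *s* | Score, Cotrifazid only |
|---|---|---|---|---|---|---|
| 0 | 0 | 86.0% | 5.9% | 5.9% | 5.9% | 4.7% |
| 2% | 0.3 | 86.2% | 6.7% | 6.6% | 6.5% | 5.3% |
| 5% | 0.7 | 86.6% | 8.0% | 7.6% | 7.3% | 6.4% |
| 10% | 1.4 | 87.2% | 10.5% | 9.6% | 8.7% | 8.5% |
| 25% | 3.5 | 89.1% | 22.4% | 18.7% | 15.5% | 18.4% |

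At *s* = 10% the Wald excess is 10.5 − 5.9 = 4.6 points. If control lost the same share it would be 8.7 − 5.9 = 2.8 points. Most of the inflation therefore comes from dropping failures at all, and the unequal rule adds the rest.

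**The case against.** **The restricted set may not be the main analysis.** Section 9 defines an intention-to-treat population first, a pair of populations is usual in a non-inferiority trial, and a statistical analysis plan may say which leads. This stands in part. A reader might infer that the protocol makes the restricted set the sole or primary analysis. It does not say so: section 10.4 assigns no test to either set, and only the reference to the final analysis points to the restricted one. The exclusion rule is nevertheless stated protocol text. A set that drops patients because they failed is badly defined even in a supporting role.

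**The imbalance may be modest.** Failure and complications are grounds for withdrawal in every arm, and standard-arm patients with fewer than 3 daily quinine doses also drop out. Cotrifazid failures after a completed course stay in. The Lariam comparison rests on silence in section 9, which may be a drafting omission. All of this stands. The text does not support reading the rule as removing Cotrifazid failures alone, or all of them.

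**The size is not known.** This stands too. Carried further, the same calculation gives 59% false non-inferiority if half of Cotrifazid failures are dropped and 95% if three quarters are. The documents neither support nor rule out such shares, so these figures should not be taken as the expected effect.

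**Conclusion.** The point holds on the wording of the protocol. Section 9, applied with sections 2.1 and 6.1, can remove early Cotrifazid failures and complications from the final efficacy analysis, and no other text counts them as failures. The bias favours a false finding of non-inferiority, because the dose rule bears more on Cotrifazid than on the standard arm.

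The size cannot be stated. It is small if few failures are switched before day 7. For shares of 2% to 25%, false non-inferiority would be 6.7% to 22.4% against a baseline of 5.9% (Wald), or 5.3% to 18.4% against 4.7% (score test). These figures assume 99 evaluable patients per arm, true success of 86% and 95%, no control failures dropped, and a decision rule that the protocol does not name. The rule should be changed, but the documents do not show that the trial's conclusion would be wrong.

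**What to change.** - **Section 9:** keep in the efficacy denominator, whatever dose was completed, every patient in any of the three arms who has a complication, clinical aggravation, rising parasitaemia or other treatment failure.
- **Section 10.4.1.1:** count that event as a treatment failure from its date, by the same clinical or parasitological criteria in all arms and whether or not treatment was changed. This includes standard-arm patients who continue their treatment. A switch for tolerance alone is not an event under this rule.
- **Reporting:** give the failure rate in the intention-to-treat population, already defined in section 9, alongside.

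The trigger should be the event and not the switch. Section 6.1 makes Cotrifazid and Lariam patients change treatment on a complication while standard-arm patients continue. Scoring the switch would therefore count the same event differently by arm, this time against Cotrifazid, in an open trial.

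The cost is a few sentences. Section 6.1 already requires a final evaluation with the reason for each withdrawal. There are no extra patients or visits and no change in care. Observed success rates may be slightly lower.
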